###### **3. Method**

###### **3.1. Trial Design**

We propose to conduct an open-label trial in which 15 individuals with PTSD receive 1 week of massed CPT combined with a single dose of psilocybin (25 mg) (Figure 1). Participants will meet criteria for a diagnosis of chronic (i.e., at least six months duration) PTSD with a Clinician-Administered PTSD Scale for DSM-5 (CAPS-5) score of 50 or higher. CPT will be provided remotely twice daily (90 minutes total) over the course of a week. On the third day of the intervention, participants will come in for an in-person (6-8 hour) psilocybin dosing session. Participants will receive a total of 12 CPT sessions, 2 psychotherapy sessions related to psilocybin (preparatory and integration sessions), and one psilocybin dosing session over 7 days. The preparatory session will be completed on day 2 of the treatment week and the integration session will be completed a day after the dosing session (day 4). ​​The primary endpoint of this study will be 1 week after the end of the treatment week (week 2). All study visits including therapy sessions and psilocybin session as well as clinical assessments, will be audio and video recorded, with all recordings preserved for research, training, adherence monitoring and quality assurance purposes. We will measure clinician-assessed PTSD symptoms via Clinician-Administered PTSD Scale for DSM-5 (CAPS-5) global severity scores at baseline, the last treatment day (day 7), and at weeks 5 and 13 (follow-up). Additional outcome measures (i.e., self-reported PTSD symptoms, depression and anxiety severity, psychological function, sleep quality) and measures of putative psychological mechanisms of change (e.g., posttraumatic cognitions, experiential avoidance) will also be measured. Participants will be followed-up weekly from week 2 until week 13 (1 week until 12 weeks post-treatment). Participants will use a commercially available wearable device (Oura Ring) to collect passive data that is relevant to mental health and well-being such as physiological signals, sleep and activity patterns. For more details on the study schedule and administration of scales, please see Table 2.

[figure not shown]

**Figure 1.** Study design with timepoints.

######

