###### **3.5. Intervention**

Participants will receive 25 mg (five capsules of 5mg) of psilocybin. The dosing session will be scheduled on day 3 of the treatment week. The study coordinator and the therapist with whom they have been completing CPT sessions will be present on site for the session. After the acute effects of the psilocybin pass, participants will be evaluated for safety and discharged home with a chaperone. The participant should have a light breakfast two hours before receiving psilocybin. Under the direct supervision of the therapist, 25 mg (5 capsules of 5 mg) of psilocybin will be swallowed. The dosing session will take 6-8 hours. Psilocybin effects usually begin 20-30 minutes after administration and peak at 90-120 minutes post-administration. Within 5-6 hours, the effects eventually subside. To minimize distraction and interruption, the participant is instructed to lie down on a couch in a room with low lighting after taking the psilocybin. To encourage inward reflection, the participant will listen to a pre-programmed selection of music during the session. A therapist specialized in providing reassurance and a safe environment will accompany the participant until the effects of the dose have passed. A physician will be available on site in case of an emergency. Moreover, the study coordinator will be at the study center during the psilocybin dosing session to support the therapist if needed. The participant must remain in the room for the whole duration of the session, regardless of intensity. Unless the participant has to communicate discomfort, ask for support from the therapist, or use the toilet, the participant should stay lying down. The therapist is to check-in on how the participant is doing every 1-2 hours following dosing. The participant will be served a light meal and fruit. The therapist will review the psilocybin administration experience with the participant 5 to 6 hours after dosing. When the therapist determines the acute effects of the psilocybin have subsided, which should occur between 6 and 8 hours after taking the dose, the participant will be discharged. The participant will be discharged from the study setting into the care of a responsible person (such as a family, friend, or chaperone) who will accompany the participant home and monitor them for 24 hours after the dose was given. Research coordinator will complete pre dose and post dose assessments. Post dose assessment will be completed after acute effects of psilocybin are resolved. Upon completion of the post-dose assessments, the participant will be assessed for safe discharge under the supervision of a designated chaperone.

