The **Dissociative Experiences Scale II (DES-II)** is a 28-item, self-report measure of dissociative experiences. Dissociation is often considered a psychological defense mechanism for victims of traumatizing events, and the scale is of particular use in measuring dissociation among people with PTSD [(75)](https://www.zotero.org/google-docs/?rwaM9V).

The **Pittsburgh Sleep Quality Index (PSQI)** is a self-rated questionnaire which assesses sleep quality and disturbances over a 1-month time interval. It consist of 19 items which are grouped into 7 components, including (1) sleep duration, (2) sleep disturbance, (3) sleep latency, (4) daytime dysfunction due to sleepiness, (5) sleep efficiency, (6) overall sleep quality, and (7) sleep medication use. Each of the sleep components yields a score ranging from 0 to 3, with 3 indicating the greatest dysfunction. The sleep component scores are summed to yield a total score ranging from 0 to 21 with the higher total score (referred to as global score) indicating worse sleep quality. In distinguishing good and poor sleepers, a global PSQI score > 5 yields a sensitivity of 89.6% and a specificity of 86.5% [(76,77)](https://www.zotero.org/google-docs/?Am3at3).

The **World Health Organization Well-Being Index, 5-item (WHO-5)** is a short and generic global rating scale measuring subjective well-being. The WHO-5 items are: (1) ‘I have felt cheerful and in good spirits', (2) ‘I have felt calm and relaxed', (3) ‘I have felt active and vigorous', (4) ‘I woke up feeling fresh and rested' and (5) ‘My daily life has been filled with things that interest me'. The respondent is asked to rate how well each of the 5 statements applies to him or her when considering the last 14 days. Each of the 5 items is scored from 5 (all of the time) to 0 (none of the time). The raw score therefore theoretically ranges from 0 (absence of well-being) to 25 (maximal well-being) [(78)](https://www.zotero.org/google-docs/?b01brn).

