The **Quality of relationships inventory (QRI)** is a self-report questionnaire used to determine the quality relationships consisting of 25 items that are evaluated on a 4-point Likert scale ranging from 1 = not true to 4 = almost always true. The 25 items yield three dimensions: Support (7 items, e.g., ‘To what extent could you turn to this person for advice about problems?’), conflict (12 items, e.g., ‘How often do you have to work hard to avoid conflict with this person?’), and depth (6 items, e.g., ‘How significant is this relationship in your life?’). The QRI takes about 5 minutes to administer [(79)](https://www.zotero.org/google-docs/?yKuTDH).

The **Inventory of psychosocial functioning (IPF)** is an 80-item self-report instrument measuring PTSD-related functional impairment in the past 30 days. There are seven functional domains evaluated: romantic relationships, family relationships, work, friendships and socializing, parenting, education, and self-care. The IPF was developed to have high content validity, to not confound PTSD symptoms and related impairment, and to not require respondent attributions regarding the cause of impairment [(80)](https://www.zotero.org/google-docs/?HTmiCY).

The **Posttraumatic Maladaptive Beliefs Scale (PMBS)** is a 15-item scale that was developed to measure maladaptive beliefs about life circumstances that may occur following trauma exposure. The scale comprises three subscales: Threat of Harm, Self-Worth and Judgment, and Reliability and Trustworthiness of Others. Scores on each subscale can be derived by summing items within each subscale. A list of subscale items and reverse-code directions are indicated on the measure. Possible scores range from 15-105, and subscale scores range from 5-35 [(81)](https://www.zotero.org/google-docs/?Ptlf2e).

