###### **3.13.5. Baseline**

Participants will complete baseline assessments one day before day 1. During this visit, baseline scores for the following items will be collected:

- Concomitant medications
- Contraceptive method review
- Columbia Suicide Severity Rating Scale (C-SSRS) since last visit
- Clinician-Administered PTSD Scale for DSM-5 (CAPS-5)
- Posttraumatic Stress Disorder Checklist for the DSM-5 (PCL-5)
- Patient Health Questionnaire-9 (PHQ-9)
- Generalized Anxiety Disorder Scale, 7-item (GAD-7)
- Dissociative Experiences Scale II (DES-II)
- Pittsburgh Sleep Quality Index (PSQI)
- Quality of Relationships Inventory (QRI)
- World Health Organization Well-Being Index, 5-item (WHO-5)
- Psychosocial Functioning (IPF)
- Posttraumatic Maladaptive Beliefs Scale (PMBS)
- Brief Experiential Avoidance Questionnaire (BEAQ)
- 24 items Multidimensional Psychological Flexibility Inventory (MPFI-24)
- Difficulties in Emotion Regulation Scale-Short Form (DERS-SF)
- Self-Compassion Scale-Short Form (SCS-SF)
- Childhood Trauma Questionnaire-short form (CTQ-SF)

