###### **7. Statistics**

###### **7.1. General Procedures and Statistical Methods**

Feasibility outcomes will be reported with descriptive statistics (i.e., counts and proportions). A minimum of 2-3 participants per month (at our single site) will be considered a sufficient recruitment rate to indicate the feasibility of a future larger multi-site trial. We will estimate the proportions of participants adherent with the protocol, that withdraw, and for data completion with a 95% CI. A full trial with this design will be deemed feasible if the lower 95% confidence limit for the rates of adherence and data completion are **≥** 80%, and if the upper limit of 95% confidence interval for the withdrawal rate is ≤ 20%. Frequencies and proportions of AEs and serious AEs will be tabulated for the total sample for each AE type. For continuous outcomes, we will report the means and standard deviations of the score and its change from baseline until the end of treatment and over the follow-up visits. We will estimate the standard deviation of PTSD severity [CAPS-5] and its within person correlation between the baseline and the end of treatment scores. The study will examine the effect size associated with psilocybin-assisted CPT in participants with PTSD, including the durability of effects on PTSD symptoms. The main analysis will be a comparison of PTSD symptoms before and after treatment. There will be analyses of changes in symptoms of depression, psychological functioning, sleep quality and PTSD severity. In week 2, the primary endpoint assessment will take place for all subjects. An independent rater not involved in therapy will administer or collect some outcome measures, and others will be based on subjects’ self-report. Baseline will be compared to the primary end point and follow up time points. This study will provide data on the impact of psilocybin in conjunction with massed CPT. Based on the outcomes, this study will primarily detect effects due to psilocybin-assisted CPT on PTSD symptoms through calculating effect sizes and significance testing. A Wilcoxon signed rank test comparing Clinician-Administered PTSD Scale for DSM-5 (CAPS-5) scores from the baseline to the primary endpoint will be the main analysis. Durability of effects will be examined by comparing changes from baseline to the assessments at 1 until 12 weeks after the final CPT session (day 7) for each PTSD subject using Friedman test, which is a non-parametric test method for repeated measures. Effects on depression symptoms, psychological functioning, trauma-related beliefs and sleep quality will also be assessed for exploratory purposes. Changes in these measures will be compared from baseline to primary endpoint for participants using Wilcoxon signed rank tests. Analyses will examine changes from baseline up to week 13 using Friedman tests. Effect sizes for the psilocybin-assisted CPT will be calculated at the primary endpoint and follow-up time points.

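### PSQI and IPF on Day 7 ask about a month that lies about three quarters before treatment, so their end-of-treatment change is diluted toward no change

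*Protocol*

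**What the plan says.** **Recall periods (protocol section 3.10.2).** The PSQI "is a self-rated questionnaire which assesses sleep quality and disturbances over a 1-month time interval". The IPF is an "80-item self-report instrument measuring PTSD-related functional impairment in the past 30 days". WHO-5 asks how well each statement "applies to him or her when considering the last 14 days". Nothing elsewhere in the protocol shortens these periods, for example to the time since the last visit.

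**Calendar.** Section 3.1 sets 12 CPT sessions, two further therapy sessions and "one psilocybin dosing session over 7 days". Section 3.5 adds: "The dosing session will be scheduled on day 3 of the treatment week". Section 3.13.5 states: "Participants will complete baseline assessments one day before day 1". Section 3.1 puts the primary endpoint one week after the treatment week, which it calls week 2.

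**Schedule (Table 2).** PSQI and IPF are given at baseline, Day 7, week 5 and week 13. WHO-5 is given at baseline, on each treatment day and then weekly from week 2.

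**Analysis (section 7.1).** For continuous outcomes the plan reports "means and standard deviations of the score and its change from baseline until the end of treatment and over the follow-up visits". Sleep quality and psychological functioning are compared between baseline and the primary endpoint by Wilcoxon signed rank tests, and over the period from baseline to week 13 by Friedman tests. Day 7 is not excluded from any of these.

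**The concern.** A change score tells us about treatment only so far as the second measurement asks about days on or after treatment. On Day 7 a one-month questionnaire asks mostly about days that the participant already rated a week earlier. The planned end-of-treatment change in sleep and functioning is then pulled toward zero by the overlap alone.

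Two consequences follow. First, the time course is distorted: a small Day 7 change followed by a larger week 5 change would look like delayed onset or growing benefit, although the same pattern arises from a constant effect as the recall window clears. Second, the schedule does not match the analysis. Section 7.1 tests these domains at week 2, where neither PSQI nor IPF is collected. That leaves Day 7 as the only early value for each scale, and it is the diluted one.

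**Working it through.** The protocol gives no figure of its own here, so the check is a count of calendar days.

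**Inputs.** Baseline = Day 0, treatment = Days 1 to 7, dose = Day 3 (sections 3.1, 3.5, 3.13.5). Window length w = 30 days for IPF, 14 for WHO-5, and 28 to 31 for PSQI (the length of a month is my assumption).

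**Formula.** If the assessment day d counts, the window runs from Day d − w + 1 to Day d and holds w − d days before Day 1. If it is left out, the window holds w − d + 1 such days.

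**PSQI and IPF on Day 7**

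| Window | Before Day 1, Day 7 counted | Before Day 1, Day 7 left out |
|---|---|---|
| 28 days | 21/28 = 75% | 22/28 = 79% |
| 30 days | 23/30 = 77% | 24/30 = 80% |
| 31 days | 24/31 = 77% | 25/31 = 81% |

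With w = 30 and Day 7 counted, the Day 7 window is Days −22 to 7 and the baseline window is Days −29 to 0. They share Days −22 to 0, which is 23 of 30 days (77%). Only Days 4 to 7, four days, come after the dosing day.

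**Size of the dilution.** Assume that answers average evenly over the window and that the true state is stable before a change of size D.
- Change starting on Day 4: 4/30 × D = 0.13 D on Day 7.
- Change starting on Day 1: 7/30 × D = 0.23 D on Day 7.
- If Day 7 itself is left out, these become 3/30 = 0.10 D and 6/30 = 0.20 D.

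**Week 5.** Four weeks after Day 7 is Day 35. A 30-day window is then Days 6 to 35, wholly after the dose, and would read the full D. A constant effect would thus appear to grow 30/4 = 7.5-fold (start on Day 4) or 30/7 = 4.3-fold (start on Day 1) between Day 7 and week 5. If the week 5 visit fell as early as Day 29, one day of the window would precede Day 1 (two if the assessment day is left out), which is negligible.

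**WHO-5**

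| Visit | Before Day 1, visit day counted | Visit day left out |
|---|---|---|
| Day 1 | 13/14 = 93% | 14/14 = 100% |
| Day 6 | 8/14 = 57% | 9/14 = 64% |
| Day 7 | 7/14 = 50% | 8/14 = 57% |
| Week 2 (Day 14) | 0/14 | 1/14 = 7% |

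**Schedule against analysis.** For PSQI and IPF, Table 2 goes from Day 7 straight to week 5. The week 2 Wilcoxon test in section 7.1 therefore has no PSQI or IPF data. Section 7.1 names domains, not scales. I read sleep quality as PSQI and functioning as IPF.

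**The case against.** The best case for leaving the plan alone is this. The study is a 15-person, single-arm feasibility trial, and section 7.1 describes the sleep and functioning analyses as exploratory. The only explicit use of an end-of-treatment change is a descriptive mean and standard deviation. The Friedman sentence does not list visits, and a visit list is something an analysis plan could settle. Respondents may also weight recent days more heavily, which would shrink the dilution. Weeks 5 and 13 are essentially free of the problem.

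Much of this stands, and it limits the weight of the point. It does not remove it. The scales, recall periods and visits are fixed in the protocol, and no analysis plan can recover what the Day 7 questionnaire does not ask. Recency weighting is possible, but the data could not reveal how much of it there was. A descriptive change is still a reported result.

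A reader might also infer more than the protocol supports:
- *That Day 7 PSQI and IPF cannot show any effect.* They can show a reduced one; the even-averaging figure is 0.13 to 0.23 of the change, not zero.
- *That WHO-5 on Day 7 mostly measures pre-treatment days.* It is about half, and WHO-5 is collected at week 2 with a clean window.
- *That daily WHO-5 scores will serve as labels for single days of Oura data.* Section 7.1 treats active data as ground truth for monitoring anxiety and depression, but nothing says that Day 1 to 7 WHO-5 values label individual days.
- *That CAPS-5 and PCL-5 share the fault.* The protocol states no recall period for either.

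**Conclusion.** The point holds for PSQI and IPF. Between 75% and 81% of their Day 7 recall window precedes treatment, and about 77% of it repeats the baseline window. No reasonable way of counting days changes that. The end-of-treatment change for these two scales is diluted toward no change. The fraction that would show, about 0.13 to 0.23, rests on even averaging over the window and is illustrative. The missing week 2 PSQI and IPF values make it matter more, because Day 7 is then the only early value.

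For WHO-5 the within-week values are diluted (half pre-treatment on Day 7, more on Days 1 to 6), but the week 2 value is not. The feasibility outcomes are unaffected, and no effect on the week 2 CAPS-5 main analysis is shown.

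**What to change.** In section 7.1:
- Name week 5 as the first post-treatment comparison for PSQI and IPF. This also resolves the week 2 test for which Table 2 collects no data on these scales.
- Remove their Day 7 values from the change and Friedman analyses. The sponsor could instead drop the Day 7 administration in Table 2, or keep it and report it only descriptively, labelled as mostly pre-treatment recall.
- For WHO-5, use week 2 (Day 14, window Days 1 to 14) as the first post-baseline comparison, in line with the stated primary endpoint, and describe the Day 1 to 7 values as diluted.

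**Cost.** This is a change of wording, with no new assessment. Dropping the Day 7 administration would spare participants the 80 IPF items on the last therapy day. The downside is that no end-of-treatment figure would be available for sleep and functioning, and the first usable value for both would come at week 5.

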**3.10.3. Exploratory Outcomes Measures**

1. Digital physiological passive data collected through the use of a wearable device (Oura Ring).
2. Digital phenotype profile (DPP):
3. Personal digital phenotype profile (pDPP) will be constructed based on the wearable and clinical assessment data.

See section (3.7) for the measures used to evaluate the effect of psilocybin-assisted CPT on digital physiological passive data collected through the use of a wearable device (Oura Ring).

###### **3.10.4. Safety Outcome Measures**

Safety measures will be applied as described below to minimize risks associated with study participation. The safety of participants will be assured before, during and after the psilocybin dosing session and during the study period by assessing physiological effects, psychological distress, concomitant medication use, medical events, spontaneously reported reactions, and suicidality. Therapists and study physician will be available via mobile phone throughout the study to ensure participant safety. Vital Signs (blood pressure, pulse, and temperature), Columbia Suicide Severity Rating Scale (C-SSRS), AEs and spontaneously reported reactions will be collected. All AEs, TEAEs, SAEs and AESIs will be collected from day 1 of treatment week until study termination. AEs may be collected during in-person visits or over the telephone or Zoom.

The **Columbia-Suicide Severity Rating Scale (C-SSRS)** is a clinician-administered measure of suicidal behavior devised to detect potential suicidal thoughts or behaviors during a clinical trial. It consists of a “Baseline” form that will assess suicidal ideation, ideation intensity, and behavior in the past 6 months, and a form for assessing current suicidal ideation and behavior. The C-SSRS consists of a series of questions and can be administered during a face-to-face interview or over the telephone. Suicidal ideation and behavior will be assessed at all visits. The C-SSRS Intensity scale for Lifetime obtained a Cronbach’s alpha of 0.93 and 0.94 for the Since Last Visit form, and Last Visit C-SSRS severity scores were positively correlated with the BDI “suicide thoughts” item [(91)](https://www.zotero.org/google-docs/?6SV43q).

**Figure 2.** Summarizes the study aims and presents the outcome measures for each aim.

[figure not shown]

